### Data Management

Data will be collected on the internet via the CompuSense platform, from which the data will be retrieved and securely stored on a password-protected university computer. These data will be transported into an SPSS file, on which data cleaning and analyses will be conducted.

All participant data will be included in the cross-sectional comparisons, provided the participants have at a minimum undergone COVID-19 swab testing (and we have obtained the result) and completed the SSTQ, SNOT-22, and in-clinic smell and taste test (SSTT). All remote data collection will use web-based forms with forced choice response questionnaires to encourage adherence to the trial protocol, and each participant will receive daily reminders to complete their home-use smell and taste test and questionnaires. Attrition rates are difficult to estimate a priori; however, participants who provide a low number of completed tests (<25%) will be excluded from the longitudinal analyses investigating the home-use testing procedure. Missing data per analysis will be deleted listwise (ie, the individual’s data will be removed from the analysis in question if a single value for any included variable is missing).

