**Assessments**								
	Baseline variables: gender, age, education status, nationality, ethnicity, employment status, smoking status, vaping status, medication, COVID-19 test result		✓					
	Primary outcome variables: COVID-19 symptoms (and onset), smell and taste acuity			✓	✓	✓	✓	✓
	Secondary outcome variables: appetite, food enjoyment, eating behaviors, nausea, weight, food-related quality of life		✓	✓	✓	✓	✓	✓

^a^SSTT: Singapore Smell and Taste Test.

^b^Participants were asked to complete the SSTT daily from Day 1 to Day 28.

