### The SSTT

Participants will be provided with their own standardized home-use smell and taste test that they will complete daily for up to 28 consecutive days (Multimedia Appendix 2). The questioning approach is based on that used in the Yale School of Medicine “Jiffy” Test of mell Sensitivity [35], in which respondents perform a similar procedure with Jif peanut butter.

The SSTT smell test includes two odors—a food odor (mango) and a nonfood odor (detergent)—both of which consist of odor mixtures that have been formulated by an international fragrance manufacturer (Symrise AG). The odor mixtures were chosen to avoid possible specific anosmias to individual odor compounds, and the odors are dosed at the suprathreshold level in specialized odor delivery pens (Otto Hut). Both fragrances have been tested to deliver a suprathreshold odor at a consistent intensity and stability for the duration of the home-use test period. To perform the test, the participants remove the pen lid and place the pen 3 inches from their nose while breathing normally. For each smell, participants will identify the smell and rate the perceived intensity on a visual analog scale (VAS) from “not strong at all” to “extremely strong smell.”

For the daily taste test, participants will be provided with small quantities of powder selected to represent the four prototypical tastes: “sweet” (table sugar, NTUC FairPrice), “salty” (table salt, NTUC FairPrice), “bitter” (granulated coffee powder, Nescafé), and “sour” (lime powder, Knorr). The participants will be instructed to take a small amount of each item in a sequential monadic order on the tip of their tongue with a small spoon; they will then be asked to identify and rate the perceived intensity of the taste on a VAS from “not strong at all” to “extremely strong taste” through a web-based questionnaire completed on their smartphone or other device. The participants will be asked to rinse with water between each taste stimulus and will be provided with sufficient taste stimuli for the 28 days of assessment.

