### Statistical Analysis

Using a case-control study design for people testing positive (case) or negative (control) for COVID-19 infection, data will be collected on changes in smell and taste loss that have occurred in the 2 weeks prior to the COVID-19 test and on smell and taste acuity changes measured on a daily basis for up to 28 days following the COVID-19 test. The data will be used for descriptive comparisons of the onset, duration, and severity of smell and taste changes with COVID-19 infection and to report on the incidence of these changes among participants testing positive for COVID-19 infection (and those recovering from infection).

Logistic regression analysis will be used to estimate the odds ratio for loss of smell and taste sensitivity as a predictor of testing positive for COVID-19 infection. This will also enable comparison of smell and taste loss as a predictor of COVID-19 infection compared to other symptoms, such as fever and dry cough. Pearson correlations will be used to investigate relationships between smell and taste changes and other symptoms. Time-series analysis of variance (ANOVA) models will be run to investigate temporal changes in smell and taste ratings over time, with baseline ratings in smell and taste acuity corrected for at an individual level. Linear mixed models will be used to test for significant differences in smell and taste acuity between groups, with participants stratified by their COVID-19 infection status.

Factor analyses, using oblique rotation and baseline home-use test responses (conducted in-clinic), will be conducted to assess the internal consistency of our smell and taste test. Adjusted odds ratios will be calculated to investigate the best predictors of recovery of smell and taste acuity postinfection. Linear regression will be run to examine whether responses to the smell and taste test predict responses to the household item odor test (smell) and self-reported taste acuity, respectively. Regression analyses will be conducted to investigate the association between loss of smell and taste acuity and self-reported appetite and food-related quality of life. All statistical analyses will be completed using SPSS (IBM Corporation).

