### Study Limitations

There is potential for poor compliance by volunteer participants in completing their daily assessments throughout all 28 days of the assessment period. To mitigate this, all questionnaires and home-use test procedures will be short and easy to complete while maintaining the scientific rigor of the test approach. Similarly, the SSTT test measures focus on detecting changes in “usual” sensory perception, and the stimuli have deliberately been selected to monitor changes in suprathreshold perceptual intensity. As such, the SSTT approach will not provide information regarding changes to smell and taste at the perithreshold level (ie, identification, detection discrimination thresholds) or profile odor identification across a wide range of odor stimuli to identify specific anosmias. Although participants will be texted daily reminders to complete their daily home-use tests, their participation is entirely voluntary, with potential for poor adherence and retention. Our proposed procedure for handling potential missing data scenarios are outlined previously (see the Data Management section).

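### The single-missing-value deletion rule is not reconciled with the 25% completion floor, and in any analysis using all 28 days it could remove a large, possibly near-total, share of participants

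*Protocol article*

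**What the plan says.** Data Management sets two rules, one after the other. The first is a floor: "participants who provide a low number of completed tests (<25%) will be excluded from the longitudinal analyses investigating the home-use testing procedure". The second covers missing data in every analysis and is listwise, explained in a parenthesis as follows: the individual's "data will be removed from the analysis in question if a single value for any included variable is missing". The unit removed is the person, and no type of analysis is exempted.

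The daily data run over four weeks. The footnote to Table 1 reads: "Participants were asked to complete the SSTT daily from Day 1 to Day 28". The section on the SSTT describes a "standardized home-use smell and taste test that they will complete daily for up to 28 consecutive days".

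Two model families in the Statistical Analysis section use these ratings. One is the ANOVA: "Time-series analysis of variance (ANOVA) models will be run to investigate temporal changes in smell and taste ratings over time". The other is the mixed model: "Linear mixed models will be used to test for significant differences in smell and taste acuity between groups". Neither sentence says which days enter or how the data are laid out.

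On adherence, Study Limitations says of the volunteers that "their participation is entirely voluntary, with potential for poor adherence and retention", and refers back to Data Management for the handling of missing data. Data Management gives no expected attrition or completion rate.

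**The concern.** The two rules serve different aims. The floor accepts that most people will miss some days and asks only for a minimum of data. The listwise rule accepts no gap at all. If the daily ratings enter as 28 variables, as in a conventional repeated-measures ANOVA, a participant with 7 to 27 tests passes the first rule and is removed by the second. The mixed model can use incomplete series, and person-level deletion gives up that advantage.

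The time course of smell and taste change is a primary objective in the Introduction and is listed again under Primary Outcomes. If that analysis rests only on participants who completed every day, it loses precision. It may also describe an unrepresentative group, because being very ill, or having recovered and lost interest, are plausible reasons for missing days.

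**Working it through.** **Inputs**
- Daily tests: 28 (Table 1 footnote).
- Floor: 25% of the tests (Data Management).
- Scale: 235 participants (Sample Size Determination). This number was set for the cross-sectional logistic regression and serves here only to turn percentages into people.
- Daily completion rate q: not given. Assumed range 0.80 to 0.99.
- Within-person correlation of missed days, rho: not given. Taken as 0 (independent days) and as 0.1 to 0.5 (clustered).

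**Step 1. The plan's own figures.** 0.25 × 28 = 7, so a participant with 7 or more tests is kept. The 235 is reproduced by a Wald-test calculation for logistic regression with a standard normal predictor and variance correction (probability 0.20, odds ratio 1.723, power 0.95, one-sided 0.05), which gives 234.6. Nothing below depends on it except as a scale.

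**Step 2. Who is left when all 28 days enter.**
- Independent days: P(all 28 complete) = q^28. For example, 0.95^28 = 0.238 and 0.238 × 235 ≈ 56.
- Clustered days: beta-binomial, P(all 28 complete) = B(a + 28, b) / B(a, b), with a = q(1 − rho)/rho and b = (1 − q)(1 − rho)/rho. For q = 0.90 and rho = 0.1, a = 8.1 and b = 0.9, which gives 0.259, or 61 of 235.

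**Step 3. Who is left under the 25% floor alone.** P(at least 7 of 28 complete), from the binomial or beta-binomial tail.

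| Daily completion q | All 28 days, independent | All 28 days, clustered (rho 0.1 to 0.5) | Floor alone (independent or clustered) |
|---|---|---|---|
| 0.99 | 75% (177) | 88% to 96% (206 to 226) | over 99% |
| 0.98 | 57% (133) | 77% to 92% (181 to 217) | 99% to 100% |
| 0.95 | 24% (56) | 51% to 82% (121 to 193) | 98% to 100% |
| 0.90 | 5% (12) | 26% to 67% (61 to 157) | 97% to 100% |
| 0.80 | 0.2% (0.5) | 6% to 44% (15 to 103) | 92% to 100% |

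**Step 4. What the second rule removes from those whom the first keeps.** At q = 0.90:
- independent days: 235 − 12 = 223 of 235
- rho = 0.1: 235 − 61 = 174
- rho = 0.5: 227 − 157 = 70

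**Step 5. When the loss is near-total.** Fewer than 10% remain only if q^28 < 0.10, that is q < 0.10^(1/28) = 0.921, with independent missed days.

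**The case against.** **The layout is not fixed.** The article names time-series ANOVA models without saying that all 28 days enter as variables. Weekly values, per-person summaries or one row per test would lose far fewer people, and a full protocol or analysis plan may settle this. This stands as a limit on the size of the loss. It does not remove the problem, because the deletion rule is worded for the individual and exempts no longitudinal analysis.

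**The rules can be run in sequence.** A reader might call them a flat contradiction. In strict logic they are not: a floor can be applied first and listwise deletion afterwards. The conflict is one of effect, and it arises where an analysis needs every day.

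**Nearly everyone is lost.** A reader might infer this, but the documents do not support it as a fact. They give no completion rate. Independence is also the harshest convenient assumption, since missed days usually cluster in the same people.

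**Few infected participants would remain.** A reader might multiply 235 by 0.20 to get a number of positive cases. The 0.20 in Sample Size Determination is a conditional probability under the null hypothesis, not an expected share of positive swabs. No count of retained cases can be derived from it.

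**The recovery curve is biased.** Nothing in the article links missed days to illness or recovery, so neither the presence nor the direction of bias is shown. It is plausible, and no more.

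**Safeguards and other analyses.** Forced-choice forms prevent skipped items within a session, and reminders may reduce missed sessions; neither excludes a missed day. The cross-sectional logistic regression, for which the 235 was calculated, has its own inclusion rule and does not need the 28 daily tests, so it is unaffected.

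**Conclusion.** The point holds for the longitudinal analyses. As written, the single-missing-value rule overrides the 25% floor in any analysis that enters all 28 days, and it discards usable data if applied at person level to the linear mixed model.

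The loss is large and possibly near-total. How large depends on three things that the article does not give: the daily completion rate, how far missed days cluster within persons, and the layout of the ANOVA. At very high completion, or with strong clustering, most participants would remain. Bias in the time-course results is a risk that depends on why days are missed. Because a primary objective is affected and Study Limitations itself foresees poor adherence, the two rules should be reconciled before analysis.

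**What to change.** 1. Limit listwise deletion to the cross-sectional analyses.
2. For the daily ratings, make the already planned linear mixed model the main longitudinal analysis: one row per completed test, day by PCR status, likelihood-based estimation, and all completed tests used.
3. Report the at-least-25% set and the all-days-complete set as sensitivity analyses, with the number of participants in each.

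The cost is a change of wording and a little more analysis work, which the planned SPSS software can handle. The small downside is reliance on a missing-at-random assumption, which is still weaker than what listwise deletion requires.

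### Listwise deletion of whole participants, applied as written to the Day 1-28 ratings, drops anyone who misses one day and makes the 25% completion threshold almost inoperative

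*Protocol article*

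**What the plan says.** The Data Management section gives two rules for incomplete data.

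- **Completion threshold:** "participants who provide a low number of completed tests (<25%) will be excluded from the longitudinal analyses investigating the home-use testing procedure". Over 28 daily tests, 25% is 7 tests.
- **Listwise deletion, per analysis:** the individual's "data will be removed from the analysis in question if a single value for any included variable is missing". The unit removed is the individual and the trigger is one value. No analysis is exempted.

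The footnote to Table 1 sets the daily schedule: "Participants were asked to complete the SSTT daily from Day 1 to Day 28". The Statistical Analysis section applies two models to these data: "Time-series analysis of variance (ANOVA) models will be run to investigate temporal changes in smell and taste ratings over time", and "Linear mixed models will be used to test for significant differences in smell and taste acuity between groups". Primary Outcomes lists onset, severity, duration and recovery of smell and taste change.

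On adherence, Data Management says "Attrition rates are difficult to estimate a priori". Study Limitations says "There is potential for poor compliance by volunteer participants in completing their daily assessments throughout all 28 days of the assessment period" and refers the reader back to Data Management for the handling of missing data.

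**The concern.** In an ANOVA across days, each day's rating is an included value for that person. Under the listwise rule, one missed day takes out the participant and all their other days. The 25% threshold points the other way: it implies that someone with 7 to 27 of 28 sessions should contribute. Forced-choice web forms limit skipped items within a session but cannot prevent a skipped session.

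A linear mixed model can use whatever days a person supplied, and that is its main advantage for a diary of this kind. The rule, read literally, gives that advantage away.

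Two things are at stake. One is precision: data that the threshold is meant to keep are discarded. The other is validity: analysing only complete diaries generally requires that missed days be unrelated to the outcome. People may stop testing because they feel ill, because they have recovered or because of their swab result, so that is doubtful here.

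**Working it through.** **Inputs from the article.** 28 daily tests (Table 1 footnote). A 25% threshold, so 0.25 x 28 = 7 tests. Minimum sample 235 (Sample Size Determination). The 235 was derived for the Day 0 logistic regression and serves here only as a denominator. It can be reproduced as 234.6 (Demidenko method with variance correction, standard normal predictor, base probability 0.20, odds ratio 1.723, power 95%, one-sided 0.05). Nothing below depends on that calculation.

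**Assumed input.** Daily completion probability q. The article gives none, so a range is shown.

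**Step 1. Independent missed days.** Share with all 28 days = q^28; number left = 235 x q^28.

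| q | q^28 | of 235 |
|---|---|---|
| 0.99 | 0.755 | 177 |
| 0.98 | 0.568 | 133 |
| 0.95 | 0.238 | 56 |
| 0.90 | 0.052 | 12 |

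Half the sample is lost when q = 0.5^(1/28) = 0.976. If, as a further assumption, 20% are swab-positive (47 of 235), the complete cases number about 35, 27, 11 and 2.

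**Step 2. Adherence that differs between people.** Let q follow a Beta(a, 1) distribution, with mean a/(a+1). Then E[q^28] = a/(a+28).

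- Mean 0.95 (a = 19): 19/47 = 40%, or 95 of 235.
- Mean 0.90 (a = 9): 9/37 = 24%, or 57 of 235.
- Mean 0.80 (a = 4): 4/32 = 12.5%, or 29 of 235.

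By simulation, more than 99% reach 7 of 28 tests in all three cases. At mean 0.90, therefore, about 76% of participants pass the 25% threshold and would then be removed by listwise deletion.

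**Step 3. Can the direction of bias be fixed?** Take 52.7% with smell loss (the pooled prevalence cited in the Introduction) and assume a median loss of 10 days from the start of follow-up, lognormal with log-scale SD 0.6. A person with k days of loss has a complete diary with probability (1 - m_loss)^k x (1 - m_normal)^(28-k), where m is the daily miss rate in each state.

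- Misses 6% when normal and 2% when lost: prevalence among complete diaries reads about 65%.
- Rates swapped: about 41 to 42%, depending on how days are counted.
- Equal rates: 53%, no bias.

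The sign depends wholly on an assumption that the article does not supply.

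**Step 4. What is not reached.** The cross-sectional set needs a swab result, the SSTQ, the SNOT-22 and the in-clinic SSTT, all tied to Day 0. The recall of changes in the two weeks before the swab is also collected on Day 0. The four weekly questionnaires are less exposed: at an assumed 0.90 per week, 0.90^4 = 66% are complete (154 of 235).

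**The case against.** The strongest reply is that the two rules have different scopes and can coexist. The threshold decides who enters the longitudinal analyses, while listwise deletion works per analysis and per included variable. With data in long format, the smell rating is one variable with many rows, and deletion would drop only the incomplete rows. The threshold itself suggests that partial completers were meant to stay. The data layout may also be set out in a full protocol that is not shown.

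Much of this stands. A reader might infer that the two rules cannot both operate; the article does not support that, because they clash only where each day counts as its own value for the person. The reply does not settle the matter, however. The stated rule removes the individual rather than the row, exempts no analysis, and has its full effect on an ANOVA that needs complete rows. A later document would have to contradict it.

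A reader might also infer that the primary results rest on a small, selected remnant. That is not established either. Adherence is unknown, and at 99% daily completion three quarters remain. Daily reminders and short tests are planned. Onset, duration and severity are assigned to descriptive comparisons that need not use complete diaries. Sample Size Determination names as primary outcome the Day 0 question of whether loss predicts a positive swab.

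Finally, it is tempting to say that loss or persistence will be overstated. Step 3 shows that the opposite is equally possible.

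**Conclusion.** The concern holds in a bounded form. The article states a person-level deletion rule that, applied as written to the Day 1-28 time-series ANOVA, discards everyone with a missed day and leaves the 25% threshold with almost nothing to do. For the mixed model, the same follows only on a literal reading.

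The size depends on assumed adherence. Between 75% and 5% of participants remain for independent daily completion of 0.99 down to 0.90, and between 40% and 12.5% for adherence that varies between people with mean 0.95 down to 0.80. Selection bias is a real possibility of unknown direction. The Day 0 analyses, including the only powered one, are largely unaffected. The wording should be corrected whatever adherence turns out to be, because an analyst cannot tell from it which participants belong in the longitudinal set.

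**What to change.** In Data Management, restrict listwise deletion to the Day 0 cross-sectional analyses. For the Day 1-28 outcomes, state that every observed person-day of participants meeting the 25% threshold enters the linear mixed model already planned, in long format and fitted by likelihood. In Statistical Analysis, use that model for change over time in place of an ANOVA that needs complete rows. Report completion by day and by swab status, so that readers can judge whether missed days relate to infection or recovery.

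The cost is a few sentences. No new data are needed, and the model is already in the plan. The downside is reliance on missing at random given the observed ratings and swab status. That assumption is weaker than the missing-completely-at-random assumption that listwise deletion generally needs.

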### Availability of Data and Materials

No data sets are included in this protocol (not applicable). The study materials (Multimedia Appendices 1-3) are provided. According to National University of Singapore guidelines, it is not possible to grant public access to a participant-level dataset. However, in the event of publication of the trial results, a full protocol, study materials, and any relevant statistical code will be made publicly available on the Open Science Framework.

